### Screening and enrolment

Data collection details are summarized in *Table* *2*. Screening will begin upon obtaining informed consent, with each participant assigned a unique screening number incorporating a site‐specific identifier. During screening, compliance with inclusion and exclusion criteria will be evaluated. Screening failures will be documented in the trial database, including reasons for non‐eligibility. If minor deviations from the criteria occur and the clinical status of a patient changes, one re‐screening may be permitted. Eligible participants meeting all criteria will proceed to randomization and intervention. The trial aimed to include 72–108 participants. To account for potential dropouts before the 30‐day intervention phase, the Steering Committee may decide to enrol additional participants. Mortality is a key safety outcome. Therefore, patients who die before completing the intervention phase will not be classified as ‘dropouts’. The total enrolment was planned to not exceed 108 participants. The trial ended on 30 January 2025. The final number of patients with complete randomization was 93.

**Table 2 ejhf3799-tbl-0002:** Trial flow chart

Description	Screening phase	Baseline	Intervention phase			Extension phase			
			Day 1 to 30			Day 31 to 60			
Timing	1–3 days before baseline		±2 days			±2 days			
Day(s)	−3 to −1	1^a^	10	20	30	31	40	50	60
Informed consent	X^b^								
Inclusion/exclusion criteria	X								
Demographic data	X								
Concomitant illness and medical history^c^	X								
Weight, height	X^d^	X^e^			X^e^				X^e^
Vital signs^f^	X^d^	X	X	X	X		X	X	X
ECG	X^d^		X	X	X		X	X	X
4 m walking test^g^	X	X	X	X	X		X	X	X
Laboratory tests^h^	X^d^	X	X		X		X		X
Echocardiography	X^d^				X				X
Performance status and QoL questionnaires^i^		X	X		X		X		X
PGA			X	X	X		X	X	X
Adverse event reporting^j^								
Randomization		X^a^							
Study treatment (optimized HF therapy/placebo)		X^k^			X				
Study treatment (HF therapy/care)						X^l^			X
Recording of changes in concomitant medication^m^	X								

ECG, electrocardiogram; HF, heart failure; PGA, patient global assessment; QoL, quality of life.

^a^
Baseline assessments will be done in the morning. Randomization will be done, and study medication will be administered immediately after completion of baseline assessments.

^b^
Informed consent has to be signed (with date and time) before any trial‐related activity.

^c^

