If neither of the patients complete their study period (due disease progression [i.e. entering the dying process] or death), an imputed observation time (day 30) will be used to assess the outcome for both patients. For patients with documented disease progression related study withdrawal, a worst‐case imputation will be performed, i.e. patients will be considered unable to wash themselves, unable to walk, or considered their health ‘much worse’ in the PGA. If precise day‐by‐day recorded data are not available for both patients, and results for the observation period are only provided as summary statistics at visit‐day 10, visit‐day 20, and visit‐day 30, then results will be calculated up to the end of their last common visit on day 10, 20, or 30, respectively, using the ‘last common visit’ approach. Under the ‘last common visit’ approach, the win criterion for the percentage of days alive and able to wash oneself is defined as a difference between two patients of >15.00% for an observation period extending to visit‐day 10, >10.00% for visit‐day 20, or >5.00% for visit‐day 30, with the patient demonstrating the higher percentage deemed the winner.

The second endpoint component, i.e. the ‘ability to walk 4 m’ (during 30‐day intervention phase), will be assessed at days 10, 20, and 30, with counts ranging from 0 to 3 visits. The patient with a higher number will be the ‘winner’. The walking ability is measured by the time taken to walk 4 m, with timing starting from the first foot movement and ending when one foot crosses the finishing line. The result is also used to calculate walking speed. For patients who die or are unable to walk, the walking speed will be recorded as zero.

The third component of the primary endpoint, i.e. ‘self‐reported PGA of subjective well‐being’, will be assessed at the last common assessment visit where both patients were alive (i.e. day 30, 20, or 10). The PGA assesses overall well‐being since enrolment on a 7‐point Likert scale ranging from ‘much worse’ to ‘much improved’. For patients who died, a value (8) ‘dead’ will be assigned. A better PGA score will be considered a ‘win’ but only if it is better than at least score of 6 (i.e. a patient needs to at least ‘moderately worse’). Pre‐specified sensitivity analyses for this win ratio include introducing all‐cause mortality as the highest‐priority component, where longer survival wins with a difference exceeding one day, and reversing the order of walking and PGA components.

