### Sample size calculation

This study aims to randomize a minimum of 72 patients who would complete the trial, with 36 patients each in the intervention and control groups. The sample size calculation is based on a two‐sided alpha level of 0.05 and a power of 85%. Assuming the number of days alive and able to wash themselves during the last 4 weeks is 11 ± 6 days (mean ± standard deviation) in the control group, the intervention is expected to improve this measure by 5 days during the 28‐day treatment period. To account for an estimated 20% dropout rate, the study anticipates retaining data from 58 patients. Power analysis, conducted using the Wilcoxon rank‐sum test at a two‐sided alpha level of 0.05, confirms 85% power for 72 enrolled and 58 completing participants (G*Power, version 3.1.9.7). Using other software packages, the power of the study under the same conditions will be 83.4% (nQuery) or 86.4% (SAS). A mean difference of 5 days and a standard deviation of 6 days results in a probabilistic index (i.e. the probability that the days alive and able to wash themselves are larger for a patient in the experimental group as compared to a patient in the control group) of 0.278. A probabilistic index of 0.278 indicates the likelihood that a patient in the intervention group will have more days alive and be able to independently wash themselves than a patient in the control group. If the intervention group achieves at least a 6‐day improvement during the treatment period of 28 days, the power of primary endpoint exceeds 90%. It should be noted that precise power calculations for this study are limited by the very restricted availability of prior data regarding test reproducibility and expected treatment effects. Of note, to account for patient dropouts during the initial 30‐day randomization phase, the protocol allowed recruitment of up to 108 patients. The final sample size was 93 randomized patients. Of note, a sample size of 46 patients per group yields a power of 80% at a two‐sided significance level of 5% given a win ratio of 2.1 and a proportion of bindings of 10%.

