The primary endpoint analysis for comparison of both treatment groups will employ the win ratio approach, without stratification.^33^, ^34^ Test statistics (Finkelstein–Schoenfeld), *p*‐values, point estimates (win ratio, win difference, win odds), and 95% confidence intervals (CI) will be calculated as specified. Secondary endpoint analyses will include the win ratio approach for ‘days alive and being able to wash themselves since baseline’, with specific win criteria for aggregated washing ability data based on common study visits. The 4 m walking ability will be analysed using a proportional odds logistic regression model at day 30, with patients who died or withdrew considered unable to walk. This model will assess the accumulated frequencies of being able to walk 4 m at 10, 20, and 30 days of follow‐up, with possible outcomes ranging from 0 to 3. PGA of well‐being will be analysed using a mixed‐effects proportional odds model with treatment, visit, treatment‐by‐visit interaction and study centre as fixed effects. Missing self‐reported PGA for deceased patients will be considered as an additional category. Odds ratio with 95% CI will be calculated at time points 10, 20, and 30 days, respectively. Overall quality of life (i.e. question 15) of the EORTC QLQ‐C15 PAL questionnaire and NT‐proBNP will be analysed using Gaussian mixed linear models for repeated measures (MMRM), fitting assessments at 10, 20, and 30 days with fixed effects for group, time, group‐by‐time interaction, baseline, and study centre, assuming a multivariate normal distribution with unstructured covariance for error terms. NT‐proBNP analyses will be on the log‐scale. Least squares means for the intervention group as well as for the difference between treatment groups will be reported with 95% CI. Data from validated scales such as ECOG Performance Status,^29^ Karnofsky Performance Status,^30^ and quality‐of‐life questionnaires^35^ will be summarized by treatment group and time point. Continuous variables (e.g. 4 m‐walking time, Karnofsky Performance Status, PPS, PPI, PaP, LVEF, eGFR) will also be analysed over time based on MMRM. Ordinal variables such as ECOG Performance Status, and PGA score at day 10 and day 20 will be analysed using proportional odds models. Safety endpoints will include adverse events classified by treatment arm. Descriptive summaries will consist of the number of subjects, percentage, and total events categorized by MedDRA system organ class and preferred term. Treatment‐emergent adverse events will be further analysed with a focus on events potentially linked to the intervention, including acute kidney injury, and symptomatic hypovolaemia and hypotension. All endpoints will be assessed in the intervention phase (day 1–30) and separately in the open‐label extension phase (day 31–60), as well as over the entire study period from baseline to day 60.

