
Cox‐proportional hazards regression model will be used to analyse all‐cause mortality. Kaplan–Meier curves with log‐rank test for group comparisons will also be computed. A hazard ratio with 95% CI will be estimated. The proportional hazards assumption will be visually checked using graphical diagnostics, including scaled Schoenfeld residuals, and by testing the time × treatment interaction. Covariates for multiple regression will include age, sex, body mass index, tumour aetiology, clinical status (ECOG, Karnofsky index, self‐care ability), presence of comorbidities (type 2 diabetes, anaemia, iron deficiency), study centre, screening NT‐proBNP level, and prior cardiovascular therapy. Measurements from TTE of local investigators and central study core lab will compared by the Bland–Altman method. The influence of dynamic allocation will be investigated using re‐randomization tests or by adding variables used in the minimization approach as fixed effects (i.e. age, sex, body mass index, tumour aetiology, clinical status [ECOG, Karnofsky index, self‐care ability], presence of comorbidities [type 2 diabetes, anaemia, iron deficiency], screening NT‐proBNP level and prior cardiovascular therapy); if convergence issues arise, variables will be dropped in order of increasing importance.

Sensitivity analyses will evaluate the robustness of results for missing data, and exploratory analyses may provide insights into ancillary objectives. All statistical calculations will be done in R (R Core Team. R: A Language and Environment for Statistical Computing, R Foundation for Statistical Computing, Vienna, Austria), SAS (SAS Institute Inc., Cary, NC, USA), SPSS (IBM Corp., Armonk, NY, USA) and Stata (StataCorp LLC, College Station, TX, USA).

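### The confirmatory PGA model has no patient-level baseline covariate, although baseline status is collected and was balanced by minimisation: the cost is power, not validity

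*Protocol article*

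**What the plan says.** The Protocol article, Statistical analysis, names the PGA model's fixed effects in full: a mixed-effects "proportional odds model with treatment, visit, treatment‐by‐visit interaction and study centre as fixed effects", with deaths as an extra outcome category and odds ratios at days 10, 20 and 30. PGA is one of four key secondary endpoints tested by the Hochberg procedure, after the primary endpoint and the washing-days endpoint have both been rejected.

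PGA has no baseline value of its own. The Primary endpoint section states: "The PGA assesses overall well‐being since enrolment". Table 2 schedules it from day 10 onward.

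Other baseline information exists. The Table 2 row "Performance status and QoL questionnaires" is marked on day 1, and its footnote lists ECOG, Karnofsky and PPS among the instruments. Another footnote places randomisation after the baseline assessments.

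At the end of Statistical analysis the article lists ECOG, Karnofsky and self-care ability among the minimisation variables. It plans to examine the influence of dynamic allocation either by re-randomisation tests or by "adding variables used in the minimization approach as fixed effects". Study centre is not on that list.

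**The concern.** Expected survival at entry is one to six months and death is a PGA category, so day-30 PGA is partly a survival outcome. Baseline performance status is then plausibly prognostic. The article treats it that way elsewhere: ECOG, Karnofsky and self-care ability are covariates in the mortality regression. The trial also took the trouble to balance the arms on these factors.

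The model that produces the confirmatory PGA p-value uses none of this information. The check on dynamic allocation does not close the gap. It is worded as a choice between two routes, so the adjusted fit may never be run. It names no endpoint, and it leaves the model behind the Hochberg step unchanged.

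At stake is power for the trial's direct measure of well-being, in a trial of 93 patients whose article lists small sample size as a limitation.

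**Working it through.** **The plan's own figures.** No power is stated for PGA. The stated calculation concerns washing days: "11 ± 6 days (mean ± standard deviation) in the control group", "the intervention is expected to improve this measure by 5 days", and "85% power for 72 enrolled and 58 completing participants". With 29 per arm, d = 5/6 = 0.833 and rank efficiency 3/π = 0.955, the noncentral t gives 86.1%; simulation of the Wilcoxon test (20,000 runs) gives 85.6%. The win-ratio statement also reproduces: σ² = 4(1 + 0.10)/[3 × 0.25 × (1 − 0.10)] = 6.52, and N = 6.52 × (1.960 + 0.842)²/(ln 2.1)² = 92.9, against 46 per group. So the stated figures are sound, but they say nothing about the PGA model.

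**Inputs for the PGA check.** From the article: 93 patients (about 46 per arm), a 7-point scale plus death giving 8 categories, five centres, visits at days 10, 20 and 30, and minimised allocation. Not in the article, hence assumed: the PGA distribution, about 20% dead by day 30, the treatment odds ratio, the minimisation probability, and above all the covariate's prognostic strength b (log-odds per SD). In a single-visit proportional odds model, b corresponds to a share of latent variance of b²/(b² + π²/3), where π²/3 = 3.29:

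- b = 0.5: 0.25/3.54 = 7%
- b = 1.0: 1/4.29 = 23%
- b = 1.5: 2.25/5.54 = 41%

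**Single-visit model, day 30.** N = 93, centre as fixed effect, conditional log odds ratio 1.1, 3,000 runs per cell; without versus with the covariate:

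| Allocation | b | Power | Loss (points) | Rejection under no effect |
|---|---|---|---|---|
| Minimised | 0.5 | 82.2% vs 85.3% | 3.1 | 5.0% vs 5.8% |
| Minimised | 1.0 | 73.8% vs 85.1% | 11.3 | 4.2% vs 5.7% |
| Minimised | 1.5 | 61.7% vs 84.3% | 22.6 | 3.1% vs 5.5% |
| Simple | 0 | 83.9% vs 83.8% | none | 6.7% vs 6.8% |
| Simple | 1.0 | 71.9% vs 83.1% | 11.2 | 6.7% vs 7.0% |
| Simple | 1.5 | 59.5% vs 81.8% | 22.3 | 6.5% vs 6.7% |

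The Monte Carlo standard error near 5% is √(0.05 × 0.95/3000) = 0.4 points. The Wald test is slightly liberal at this size, so the columns should be compared with each other rather than with 5%. With a three-level, ECOG-like version of the covariate under minimisation, the gains shrink to 84.5 − 82.2 = 2.3, 82.5 − 73.8 = 8.7 and 80.4 − 61.7 = 18.7 points.

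A second single-visit simulation used 46 per arm, 22% dead, odds ratio 2.7, arms paired on a noisy baseline score, likelihood-ratio tests and 1,500 runs. It gave power of 68.9% vs 76.9% at 16% of latent variance and 59.9% vs 76.1% at 30%. Rejection under no effect was 4.3% vs 5.7% and 3.3% vs 5.3%.

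**Three-visit models with a patient random intercept.** These are closer to the planned analysis.

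- With absorbing death, 46 per arm, paired allocation and 1,000 runs: power 77.5% vs 81.0% at b = 0.7 (3.5 points) and 78.0% vs 85.4% at b = 1.0 (7.4 points). Rejection under no effect was 5.8% vs 6.0% and 5.4% vs 6.1%, with a standard error of about 0.7 points.
- Without absorbing death, 92 patients, random-intercept SD 1.5, true log odds ratio 1.0 and 300 runs: power 67% vs 76% at b = 0.87 (9 points) and 58% vs 76% at b = 1.2 (18 points). The mean estimated log odds ratio was 1.01 both without and with the covariate. The standard error of each power figure is about 2.5 to 3 points.

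**Reading the results.** Every simulation with a prognostic covariate shows a power gain from adjusting. Lower rejection under no effect appears only in single-visit models with balanced allocation; it is absent under simple allocation and in the mixed model that checked it.

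**The case against.** The strongest reply is that the plan is coherent and the point is one of efficiency only.

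- *Attenuation.* A reader might infer that leaving out baseline status pulls the PGA odds ratio towards 1. That holds for a single-visit model. The planned model is mixed-effects over three visits. If its random effect is a patient intercept, the omitted covariate is absorbed there, and the simulated estimate did not move (1.01 vs 1.01). This objection stands in full.
- *Conservatism.* A reader might infer that the test is conservative because death is a category and no covariate enters. Those two facts do not produce it. It needs balance on the omitted factor, and even then it was not seen in the three-visit check. In the 16% scenario, 4.3% with a standard error of about 0.5 cannot be told apart from 5%. It remains possible, not shown.
- *Consistency.* The baseline term in the quality-of-life and NT-proBNP models is naturally read as each outcome's own baseline, which PGA lacks. The walking model names no covariates and the primary win ratio is unstratified. So there is no internal contradiction, and none is claimed.
- *Already handled.* Either planned check on dynamic allocation would address the size of the test under minimisation. That stands for validity. A re-randomisation test does not by itself recover the lost precision, and the adjusted route is optional.
- *Size and consequence.* PGA measures perceived change, and the article does not show that baseline status predicts it strongly. PGA is also tested only after two earlier rejections, so unconditional power overstates the practical cost. Both stand.
- *Condensed article.* Finer covariate detail may sit in an analysis plan that is not shown. But this article states the model's fixed effects, so the point concerns a stated model and not a missing detail.

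**Conclusion.** The concern holds as a loss of efficiency in a stated confirmatory model. It is not a bias, not an inflated type I error and not a contradiction.

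The loss in day-30 power is about 3 points if the covariate is weak (b = 0.5, single-visit model). If it is moderate to strong, the loss is about 4 to 18 points in three-visit random-intercept models and up to about 22 to 23 points in single-visit models. If the covariate is unrelated to PGA, there is no loss, and adjusting costs essentially nothing. These figures rest wholly on assumed prognostic strength, PGA distribution, death rate and treatment effect; the documents fix none of them. In the minimised single-visit runs, part of the gap reflects different rejection rates under no effect. The simple-allocation runs, where those rates nearly match, show gaps of similar size.

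**What to change.** Before unblinding, add to the mixed-effects proportional odds model for PGA a small pre-specified set of baseline fixed effects taken from the minimisation factors, for example Karnofsky or ECOG, plus self-care ability. State that the day-30 p-value entering the Hochberg step comes from this model. Keep the centre-only model as supportive. Do not add all twelve minimisation variables: with 93 patients and eight outcome categories that invites the convergence problems the article already anticipates.

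The cost is about one sentence and no new data. One small downside should be stated with the result: the odds ratio becomes conditional on baseline status and is not directly comparable with one from the centre-only model.

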## Discussion

End‐stage cancer patients often experience reduced physical performance, dyspnoea, severe impairment of health status and sudden death. Cardiac wasting is a hallmark of advanced‐stage cancer and has been observed in both preclinical models^4^, ^36^ and clinical studies.^37^, ^38^ The EMPATICC trial aims to address a critical gap in the management of end‐stage cancer patients by assessing an optimized therapeutic regimen, including sacubitril/valsartan, ivabradine, intravenous iron, and sodium–glucose co‐transporter 2 inhibitor, tailored to alleviate HF‐like symptoms. By investigating the effects of optimized HF therapy on patient‐centred outcomes, this trial has the potential to redefine the management strategies for a highly vulnerable population with complex needs.

Cancer cachexia is a syndrome marked by skeletal and cardiac muscle wasting, systemic inflammation, neurohormonal activation, and energy imbalance.^38^ General cachexia can contribute to progressive myocardial atrophy (i.e. cardiac wasting), LV dysfunction and ultimately HF.^21^ In advanced cancer, neurohormonal activation, inflammatory cytokines (such as tumour necrosis factor and interleukin‐6), elevated sympathetic activity, and localized wasting processes potentially contributing to myocardial and mitochondrial cell death and potentially cardiac wasting might associate with poor health care status in these patients.^6^, ^38^, ^39^, ^40^ These changes often mimic or accelerate typical HF pathophysiology, even in absence of pre‐existing cardiac disease (*Figure* *2*).

**Figure 2 ejhf3799-fig-0002:**
[figure not shown]
Intersection between cancer cachexia, heart failure and cardiac atrophy. IL‐6, interleukin‐6; QoL, quality of life; RAAS, renin–angiotensin–‐aldosterone system; SNS, sympathetic nervous system; TNF, tumour necrosis factor.

Despite the well‐documented cardiotoxicity associated with certain anti‐cancer therapies,^21^ such as anthracyclines^41^ and tyrosine kinase inhibitors,^42^ the intersection of cancer cachexia and HF pathophysiology remains poorly understood.^13^ As of now, no studies have evaluated whether therapies improving healthcare status and outcomes in HF can improve dyspnoea, or enhance quality of life in palliative care settings of cancer patients. The current study hypothesizes that the contemporary therapeutic regimen will alleviate dyspnoea and improve physical performance, enhancing self‐care capabilities and self‐reported health status in this patient population.

The EMPATICC trial is randomized and double‐blind, thus entails a low risk of bias (due selection, performance, and detection). Due to the short intervention period of 30 days, low loss to follow‐up (i.e. attrition) is expected. An open‐label extension will follow the double‐blind phase, enabling all participants, including those initially randomized to standard care, to receive optimized medical treatment. Thus, more data on sustainability of treatment effects can be obtained in a more pragmatic setting. This approach balances the rigour of a randomized controlled trial with insights gained from a real‐world application, thereby enhancing the generalizability of the findings. All interventions will be administered at approved doses under close clinical supervision to ensure safety. While many participants will be treated in oncology or palliative care wards, ambulatory patients will receive home visits to minimize the burden of travel.

One of the key strengths of this trial is its emphasis on patient‐reported outcomes, particularly those that focus on quality of life. This is especially relevant in palliative care, where the ability to maintain hygiene, such as independently washing oneself, reflects both physical and emotional well‐being.^43^, ^44^ The selection of this unique endpoint highlights the commitment of the trial to patient‐centred care and the prioritization of interventions that directly enhance the everyday functionality and dignity of the patients. Previous studies have predominantly focused on overall survival, often neglecting aspects such as everyday functionality and patient dignity.^32^ The EMPATICC trial prioritizes patient experience, acknowledging the significant impact that even modest improvements in self‐care capabilities can have on overall quality of life. This is done in a win ratio test procedure,^33^, ^34^ which combines several endpoints in one instead of analysing several primary endpoints, which would also have been an option.^32^ Currently, no studies have investigated whether HF‐specific therapies can attenuate cardiac wasting, alleviate dyspnoea, or enhance quality of life in a palliative cancer setting for cancer patients. This trial is intended to demonstrate that mitigating dyspnoea and improving physical performance will restore essential aspects of self‐care, such as the ability to maintain personal hygiene. By addressing these critical factors, the trial aims to fulfill the need to enhance patient autonomy and preserve dignity in context of advanced cancer.

This study builds on prior research exploring HF interventions and advances the field by targeting a novel patient population. The pathophysiology of cardiac wasting in cancer shares parallels with HF,^4^ offering a mechanistic justification for the application of known HF drugs in this scenario. However, the unique challenges faced by this cohort, such as frailty and polypharmacy, warrant tailored approaches to delivery of care. This trial aims to provide evidence for the safety and efficacy of HF‐directed therapies in palliative cancer care. The findings from this trial could pave the way for integrating HF therapies into the routine management of end‐stage cancer patients.

Several limitations of the design of this proof‐of‐concept trial should be acknowledged. First, the small sample size reduces the power to detect clinically important differences. Second, the short follow‐up period limits the evaluation of long‐term safety and efficacy outcomes. Third, the heterogeneity of the cancer population may introduce variability in treatment response. Lastly, self‐reported functional capacity as the primary endpoint may introduce variability due to differences in patient interpretation and reporting. Large scale studies with longer follow‐up durations are warranted to evaluate these outcomes in this population. Nonetheless, the inclusion of novel, patient‐centred outcomes ensures that the findings will remain highly relevant to clinical practice despite these limitations.

In conclusion, the EMPATICC trial will provide important evidence on the impact of optimized HF therapy in end‐stage cancer patients. By incorporating a personalized, multipronged treatment approach, this trial aims to fill gaps in palliative care management. Its novel focus on patient‐centred endpoints, such as the ability to perform basic self‐care tasks like washing oneself, highlights a unique commitment to improving the quality of life and functionality in this vulnerable population. These insights could inform future clinical practices and guidelines for improving functional capacity and quality of life in this vulnerable population.
